## Abstract

**Background:**

Administration of abciximab during primary percutaneous coronary intervention is an effective adjunctive therapy in the treatment of patients with ST-segment elevation myocardial infarction. Recent small-scaled studies have suggested that intracoronary administration of abciximab during primary percutaneous coronary intervention is superior to conventional intravenous administration. This study has been designed to investigate whether intracoronary bolus administration of abciximab is more effective than intravenous bolus administration in improving myocardial perfusion in patients with ST-segment elevation myocardial infarction undergoing primary percutaneous coronary intervention with thrombus aspiration.

**Methods/Design:**

The Comparison of IntraCoronary versus intravenous abciximab administration during Emergency Reperfusion Of ST-segment elevation myocardial infarction (CICERO) trial is a single-center, prospective, randomized open-label trial with blinded evaluation of endpoints. A total of 530 patients with STEMI undergoing primary percutaneous coronary intervention are randomly assigned to either an intracoronary or intravenous bolus of weight-adjusted abciximab. The primary end point is the incidence of >70% ST-segment elevation resolution. Secondary end points consist of post-procedural residual ST-segment deviation, myocardial blush grade, distal embolization, enzymatic infarct size, in-hospital bleeding, and clinical outcome at 30 days and 1 year.

**Discussion:**

The CICERO trial is the first clinical trial to date to verify the effect of intracoronary versus intravenous administration of abciximab on myocardial perfusion in patients with ST-segment elevation myocardial infarction undergoing primary percutaneous coronary intervention with thrombus aspiration.

**Trial registration:**

ClinicalTrials.gov NCT00927615

## Background

ST-segment elevation myocardial infarction (STEMI) is generally caused by rupture or erosion of atherosclerotic plaque and subsequent platelet aggregation and thrombosis, resulting in acute occlusion of a coronary artery [1,2]. The preferred treatment strategy consists of prompt reperfusion therapy by means of primary percutaneous coronary intervention (PCI) [3-5]. However, despite optimal reperfusion of the infarct-related coronary artery, impaired myocardial perfusion is still present in a significant proportion of patients following successful PCI, which is associated with larger infarct size and increased long-term cardiac mortality [6,7].

One of the major causes of impaired myocardial reperfusion is embolization of atherothrombotic material including platelet aggregates into the distal microcirculation [8]. In recent years, the implementation of adjunctive mechanical and pharmacological therapies during primary PCI, including manual thrombus aspiration and glycoprotein (GP) IIb/IIIa inhibitors, has significantly reduced the occurrence of distal embolization and improved clinical outcome in STEMI patients [9-15]. Several trials and meta-analyses have demonstrated that manual thrombus aspiration improved myocardial reperfusion in patients presenting with STEMI and was associated with improved survival compared to conventional PCI at clinical follow-up up to 1 year [11,12,16-20]. However, a major limitation of thrombus aspiration is its inability to prevent microvascular obstruction that has occurred prior to PCI or that has been induced by primary PCI including thrombus aspiration itself. Adjunctive pharmacological therapies are therefore needed to target these sources of microvascular obstruction.

Anti-platelet therapy is an important cornerstone of modern STEMI management. During PCI, the use of GP IIb/IIIa inhibitors improves microvascular reperfusion [13,14]. In large randomized trials, intravenous (IV) administration of the GPIIb/IIIa inhibitor abciximab during PCI was associated with a significant reduction in short- and long-term mortality and reinfarction rates in patients with STEMI [9,10,15]. An alternative approach with the use of bivalirudin instead of the combination of unfractionated heparin and a GPIIb/IIIa inhibitor has been advocated and investigated [21]. Although this may result in a lower rate of bleeding complications, a major drawback seems to be the higher incidence of stent thrombosis.

Abciximab is the Fab fragment of the chimeric monoclonal antibody 7E3, which acts as a potent platelet aggregation inhibitor mainly by binding to the GP IIb/IIIa receptor on the surface of activated human platelets. Hereby, abciximab inhibits the final common pathway for platelet aggregation by preventing the binding of fibrinogen and von Willebrand factor to activated platelets [22]. A receptor occupancy study reported that the absolute number of free GP IIb/IIIa receptors was decreased in patients with successful restoration of myocardial perfusion who were treated with GP IIb/IIIa inhibitors [23]. Experimental studies have reported additional dose-dependent anti-platelet and anti-thrombotic effects of abciximab, which is not only able to prevent thrombus formation, but also to facilitate the dispersal of newly formed platelet aggregates by displacement of platelet bound fibrinogen with higher local drug concentration, and to inhibit platelet-induced thrombin generation [22,24,25]. In contrast to other GP IIb/IIIa inhibitors, abciximab has also distinct non-GP IIb/IIIa-related properties that may reduce inflammatory pathways and reperfusion injury [26]. These dose-dependent anti-platelet, anti-thrombotic and anti-inflammatory features of abciximab suggest that a higher local platelet inhibitor concentration may translate into further clinical improvements. Higher local concentrations can be obtained by the direct administration of abciximab into the infarct-related artery.

Intracoronary (IC) administration of abciximab has been investigated in several case reports and clinical studies [27-35] (Table 1). A retrospective study suggested a significant clinical benefit of IC administration, showing a 50% reduction of major adverse cardiac events (MACE) in patients with acute coronary syndromes treated with IC abciximab compared to IV abciximab [34]. A small prospective randomized trial showed a greater degree of myocardial salvage, better recovery of left ventricular function, and improved myocardial perfusion in patients with STEMI treated with IC abciximab [27]. Thiele et al [33] reported a reduced infarct size and extent of microvascular obstruction, and improved perfusion in patients treated with an IC bolus of abciximab. In addition, there was a trend towards a clinically relevant reduction in the incidence of MACE in patients treated with IC abciximab (5.2% vs. 15.6%, p = 0.06).

**Table 1 T1:** Studies comparing IC and IV administration of abciximab in patients with STEMI

**Author**	**Year***	**Design**	**Patients**	**No**	**In favor of**	**Main results**
Wohrle et al [34]	2003	retrospective	STEMI/NSTEACS	403	IC	reduced incidence of MACE at 30 days
Bellandi et al [27]	2004	prospective, randomized	STEMI	45	IC	higher salvage index and LV functional recovery (serial gated SPECT)
Romagnoli et al [32]	2005	prospective, matched	STEMI/NSTEACS	74	IC	increased coronary flow (cTFC)
Galache et al [29]	2006	prospective, randomized	STEMI/NSTEACS	137	neutral	no difference in the incidence of MACE at 1 year
Thiele et al [33]	2008	prospective, randomized	STEMI	154	IC	reduced infarct size and extent of MO (MRI at 2 days)
Dominguez-Rodriguez et al [28]	2009	prospective, randomized	STEMI	50	IC	larger reduction in soluble CD40 ligand

* Year of publication

cTFC: corrected TIMI frame count; IC: intracoronary; IV: intravenous; MACE: major adverse cardiac event; MO: microvascular obstruction; MRI: magnetic resonance imaging; No: number of patients; NSTEACS: non-ST-elevation acute coronary syndrome; SPECT: single photon emission computed tomography; STEMI: ST-segment elevation myocardial infarction

Given the limited number of patients included in these trials, a larger randomized clinical trial is required to verify the effect of IC abciximab administration in STEMI patients undergoing primary PCI. Furthermore, there is at the present time no information with regard to the combined strategy of thrombus aspiration and IC use of abciximab. Therefore, we intend to determine the effect of IC bolus administration of abciximab on post-procedural myocardial perfusion compared to IV bolus administration in STEMI patients undergoing primary PCI with thrombus aspiration.

## Methods/Design

The CICERO trial is a single-center, prospective, randomized trial with blinded evaluation of endpoints (Figure 1). A total of 530 patients with STEMI undergoing primary PCI are randomly assigned to either an IC or IV bolus of weight-adjusted abciximab (0.25 mg/kg body weight, ReoPro 2 mg/ml, Centocor B.V., Leiden, the Netherlands). Randomization is performed by means of sealed envelopes at the catheterization laboratory when a decision to perform PCI is taken. The study takes place at a high-volume university hospital center providing 24-hours emergency cardiac care with 7 referral hospitals in a region with 750,000 inhabitants. The study was approved by the institutional committee on human research of the University Medical Center of Groningen and is in compliance with the declaration of Helsinki. The protocol of this trial has been registered at ClinicalTrials.gov (NCT00927615).

**Figure 1 F1:**
[figure not shown]
**The CICERO trial flow chart**. IC: intracoronary; IV: intravenous; PCI: percutaneous coronary intervention; STEMI: ST-segment elevation myocardial infarction.

### Study population

All consecutive STEMI patients who are candidates for primary PCI are considered eligible for participation. The inclusion criterion is a diagnosis of STEMI as defined by chest pain suggestive for myocardial ischemia for at least 30 minutes before hospital admission, time from onset of symptoms of less than 12 hours, and an ECG with new ST-segment elevation in 2 or more contiguous leads of ≥0.2 mV in leads V2-V3 and/or ≥0.1 mV in other leads or a new-onset left bundle branch block. Exclusion criteria are rescue PCI after thrombolytic therapy, need for emergency coronary artery bypass grafting, presence of cardiogenic shock, known existence of a life-threatening disease with a life expectancy of less than 6 months, inability to provide informed consent, age below 18 years, and contra-indications for the use of abciximab, which include active internal bleeding, history of stroke within 2 years, recent major surgery or intracranial or intraspinal trauma or surgery within 2 months, intracranial neoplasm, arteriovenous malformation or aneurysm, bleeding diathesis, severe uncontrolled hypertension, thrombocytopenia, vasculitis, hypertensive or diabetic retinopathy, severe liver or kidney failure, and hypersensitivity to murine proteins.

### Treatment

During PCI, the initial treatment step consists of manual thrombus aspiration whenever possible. Thrombus aspiration is performed with the Export aspiration catheter (Medtronic Inc., Santa Rosa, USA) as previously described [11]. Continuous manual suction is performed using a proximal-to-distal approach, which is defined as active aspiration during initial passage of the lesion. In patients assigned to IC administration, a bolus of abciximab is administered through the guiding catheter proximal to the lesion in the infarct-related artery over a period of 1 minute after restoration of anterograde flow. As final step a stent is implanted. Additional pre- or postdilatation with a balloon may be required in certain patients.

Patients are pre-treated with aspirin (500 mg), heparin (5000 IU IV), and high-dose clopidogrel (600 mg orally) after electrocardiographic confirmation of STEMI, usually in the ambulance. IC administration of nitroglycerine (400 μg) is administered during the procedure at the operator's discretion. During PCI, additional low-dose weight-adjusted heparin is administered as guided by the activated clotting time (target: 200 - 250 seconds). Sheaths are removed immediately at the end of the PCI procedure using the Angio-Seal device (St. Jude Medical, Inc, St. Paul, MN, USA) or by manual compression after arrival at the coronary care unit. In the setting of STEMI, the femoral approach is preferred. The radial approach is reserved for patients without femoral access. In case of radial access, sheaths are removed immediately following the PCI procedure. In patients with atrial fibrillation, a large dyskinetic area of the left ventricle, and in immobile patients, low-molecular-weight heparin is given for 1 to 3 days after sheath removal. Standard therapy after PCI includes aspirin (80 mg), clopidogrel (75 mg), beta-blockers, lipid lowering agents, and angiotensin converting enzyme inhibitors or angiotensin II receptor blockers, according to current international guidelines [36].

### Electrocardiography

A standard 12-lead electrocardiogram (ECG) is acquired at the time of presentation and at 30 to 60 minutes after the end of procedure. Times of onset of symptoms, admission, first intracoronary intervention, end of PCI and ECG recordings are registered. The magnitude of ST-segment deviation is measured 60 ms from J-point. The first post-intervention ECG at 30 to 60 minutes is classified by comparison of the ST-segments with those of the ECG at presentation. ST-segment elevation resolution is categorized as complete (>70%), partial (30-70%), or absent (<30%) [6]. On the post-interventional ECG, residual ST-segment deviation is calculated as the sum of residual ST-segment elevation and depression in all leads [37]. New-onset of Q waves on the post-interventional ECG is defined as an initial negative deflection of the QRS complex of >0.1 mV and >40 ms in an ECG lead related to the myocardial area of infarction together with all pathological Q waves. All ECG recordings are analyzed by a physician blinded to treatment allocation and clinical data.

### Coronary angiography

The following baseline, peri- and post-procedural angiographic features are recorded: the presence of thrombus and collaterals, Thrombolysis In Myocardial Infarction (TIMI) flow grades, myocardial blush grade (MBG), and the presence of angiographically visible distal embolization. TIMI flow grades are estimated as previously described [38]. Thrombus is assessed according to the criteria summarized by Mabin et al [39]. These criteria include the presence of an intraluminal central filling defect or lucency surrounded by contrast material that is seen in multiple projections, the absence of calcium within the defect; and persistence of contrast material within the lumen. Collaterals are assessed according to Rentrop's classification [40]: 0 = none, 1 = filling of side branches only, 2 = partial filling of the epicardial segment, 3 = complete filling of the epicardial segment. Evaluation of MBG is performed as described by van 't Hof et al [7]: 0 = no myocardial blush, 1 = minimal myocardial blush or contrast density, 2 = moderate myocardial blush or contrast density, but less than that obtained during angiography of a contra- or ipsilateral non-infarct-related coronary artery, and 3 = normal myocardial blush or contrast density, comparable with that obtained during angiography of a contra- or ipsilateral non-infarct-related coronary artery. Persisting myocardial blush ("staining") suggests leakage of contrast medium into the extravascular space and is graded 0. In addition, MBG is quantified with the Quantitative Blush Evaluator (QuBE) as described by Vogelzang et al [41], which provides a computer-assisted and more operator-independent score by calculating the increase and decrease of myocardial contrast density in the myocardial area of interest. Distal embolization is considered to have occurred if new circumscribed filling defects and/or abrupt cutoff of the vessel distal to the target lesion appears [42,43]. The coronary angiograms are analyzed by a physician who is blinded to treatment allocation and clinical data.

### Infarct size

Infarct size is estimated by serial measurements of cardiac markers including creatinine kinase (CK), myocardial band fraction of CK (CK-MB), lactate dehydrogenase (LDH), and troponin T. Blood is sampled at baseline and at 3, 6, 9, 12, 18, 24, and 48 hours after PCI. Peak release, time to peak release as well as area under the curve is determined. Marker levels are determined on a Hitachi 717 automatic analyzer according to the International Federation of Clinical Chemistry (IFCC) recommendation.

### End points assessment

The primary end point is the incidence of ST-segment resolution >70% as assessed on the ECG acquired 30 to 60 minutes after PCI compared to the ECG at presentation.

Secondary end points include:

- Angiographic end points: post-procedural TIMI flow, MBG (by visual estimation and with the QuBE program) and angiographically visible distal embolization

- Electrocardiographic end points: residual ST-segment deviation 30 to 60 minutes after the procedure

- Enzymatic infarct size

- Mortality and Major Adverse Cardiac Events (MACE, a combined end point of target vessel revascularization, reinfarction, and cardiovascular mortality) at 30 days and 1 year.

A safety endpoint consists of in-hospital bleeding complications.

Furthermore, the primary and secondary endpoints are to be analyzed in pre-specified subgroups, which are defined as:

1. Age (<65 versus >65 years)

2. Gender

3. Presence of diabetes

4. Number of diseased vessels (multi-vessel versus single vessel)

5. Infarct-related artery (left anterior descending artery (LAD) versus non-LAD)

6. Ischemic time (<3 versus >3 hours)

7. Angiographic presence of thrombus

8. Pre-procedural TIMI flow

9. Post-procedural TIMI flow

10. Post-procedural myocardial blush grade

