#### Statistical analysis

All statistical analyses will be performed according to the intention-to-treat principle for the overall population as well as for the pre-specified subgroups. Statistical significance is considered as a two-tailed p value less than 0.05. The Statistical Package for the Social Sciences (SPSS Inc., Chicago, IL, USA) version 16.0.2 will be used for all statistical analyses. Differences between group means will be assessed with the two-tailed Student's t-test. Chi-square analysis or Fisher's exact test will be used to test differences between proportions. Survival will be calculated by the Kaplan-Meier product-limit method. Chi-square analysis will be used to assess the relation between an individual variable and end points. The Mantel-Cox (or log-rank) test will be used to evaluate differences in survival between the two treatment groups. The Cox proportional-hazards regression model will be used to calculate relative risks and to adjust for differences in baseline characteristics.

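### Subgroups 9 and 10 (post-procedural TIMI flow and blush grade) are outcomes of the randomised treatment, so comparing IC with IV inside them is not protected by randomisation

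*Protocol article*

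**What the plan says.** Under End points assessment, the protocol article lists among the secondary end points: "Angiographic end points: post-procedural TIMI flow, MBG (by visual estimation and with the QuBE program) and angiographically visible distal embolization". The same section then states: "Furthermore, the primary and secondary endpoints are to be analyzed in pre-specified subgroups". Ten subgroups follow. Item 9 is post-procedural TIMI flow and item 10 is "Post-procedural myocardial blush grade". Item 8, pre-procedural TIMI flow, is the baseline counterpart of item 9, but the list does not separate baseline factors from outcome factors. Nothing shown marks items 9 and 10 as descriptive.

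Under Statistical analysis, all analyses follow the "intention-to-treat principle for the overall population as well as for the pre-specified subgroups".

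Three other places fix the timing and the aim:
- Methods/Design: "Randomization is performed by means of sealed envelopes at the catheterization laboratory when a decision to perform PCI is taken".
- Treatment, for the IC arm: the bolus is given "over a period of 1 minute after restoration of anterograde flow", and then "As final step a stent is implanted".
- Background: "we intend to determine the effect of IC bolus administration of abciximab on post-procedural myocardial perfusion".

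**The concern.** A subgroup comparison is a randomised comparison only if the subgroup was settled before the assigned treatment could influence it. Items 9 and 10 do not meet that condition. If IC dosing improves blush, some patients who would have had poor blush under IV dosing move into the good-blush stratum under IC. The patients who move tend to be worse than those already in the good stratum and better than those left in the poor one. The IC arm then looks sicker in both strata, whatever the drug does to ST resolution.

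At stake is how these two subgroups are interpreted. A diluted or negative within-stratum difference would carry the authority of a pre-specified, intention-to-treat analysis although it is not a randomised comparison.

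**Working it through.** **Timing and role.** No figure in the protocol rests on this point, so there is nothing to reproduce first. The passages settle the structure:

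1. Randomisation takes place when PCI is decided on (Methods/Design).
2. The IC bolus comes after flow is restored and before the stent (Treatment). Post-procedural readings are therefore later than randomisation in both arms and later than the bolus in the IC arm.
3. The same two variables are named as end points and as subgroup factors (End points assessment).
4. All primary and secondary end points are to be analysed in every subgroup. As written, this includes blush within blush grades and TIMI flow within TIMI grades. Within a single grade such a comparison has no content.
5. Intention to treat fixes the arm in which a patient is counted. It does not fix the stratum.

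**Size of the bias for blush.** The protocol gives no blush rates, so all inputs below are assumptions, except the 56.6% reference rate and the 25% increase (Sample size estimation). Read as relative, the target is 56.6% × 1.25 = 70.75%, a gain of 14.15 points. All differences are IC minus IV in percentage points of ST resolution >70%.

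*Model A: shared latent prognosis.* Blush and ST resolution are thresholds on two normal variables with correlation ρ. Good blush is 40% with IV and 40%, 50% or 55% with IC. ST resolution is 56.6% with IV; with IC it is either 56.6% (no effect) or 70.75%. There were 4 million simulated patients per scenario.

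| ρ | Good blush, IV → IC | No true effect: good / poor stratum | True gain 14.15: good / poor stratum |
|---|---|---|---|
| 0.3 | 40 → 40% | -0.1 / 0.1 | 12.4 / 15.3 |
| 0.3 | 40 → 50% | -1.8 / -1.9 | 11.0 / 13.5 |
| 0.3 | 40 → 55% | -2.8 / -2.9 | 10.2 / 12.5 |
| 0.5 | 40 → 40% | 0.0 / 0.0 | 11.0 / 16.3 |
| 0.5 | 40 → 50% | -3.2 / -3.4 | 8.7 / 13.0 |
| 0.5 | 40 → 55% | -4.8 / -5.3 | 7.5 / 11.2 |
| 0.7 | 40 → 40% | 0.0 / 0.0 | 8.6 / 17.9 |
| 0.7 | 40 → 50% | -4.3 / -5.2 | 6.1 / 12.7 |
| 0.7 | 40 → 55% | -6.4 / -8.0 | 4.8 / 9.9 |

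When the route leaves blush unchanged, the strata average back to the overall effect (ρ = 0.3: 0.4 × 12.4 + 0.6 × 15.3 = 14.1). Once the route changes blush, both strata fall below 14.15, so no weighted average of them can recover it. Part of the lower figure for good blush is already present at 40 → 40%. The bias is the further fall from that row.

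*Model B: logistic, with unmeasured injury U (standard normal).* T = 1 for IC; b = 0.4 or 0.8; g = 1.0 or 1.5.
- logit P(blush grade 3) = -0.2 + bT + gU. This gives about 46% with IV and 54 to 62% with IC.
- logit P(ST resolution) = -0.4 + 1.2 × (blush grade 3) + dT + gU.
- For the no-effect case, logit P(ST resolution) = 0.4 + 1.5U.

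Results by numerical integration:

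| Scenario | Overall | Within the two blush strata |
|---|---|---|
| Bolus acts only through blush (d = 0) | +1.7 to +4.1 | -1.2 to -3.8 |
| Direct effect added (d = 0.6) | +10.5 to +14.4 | +4.6 to +10.8 |
| No effect on ST resolution | 0 | -1.7 to -4.4 |

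**Comparison with chance error.** Assume 1:1 allocation and a half-and-half split by blush: 530 / 4 = 132.5 patients per arm per stratum. The standard error of a difference near 56.6% is √(2 × 0.566 × 0.434 / 132.5) = 0.061, about 6 points. The largest no-effect bias in Model B is 4.4 / 6.1 = 0.7 standard errors; in Model A it is 8.0 / 6.1 = 1.3.

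**The case against.** The strongest reply is that little depends on these two analyses. The primary comparison uses all randomised patients, and no sample size or success rule rests on a subgroup. The overall secondary and safety comparisons and the clearly baseline subgroups are untouched. This stands, and it limits the severity.

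A reader might also infer that the two subgroups will erase the effect or reverse its sign. The documents do not support that. Among the scenarios run, reversal appeared only where the bolus acts solely through blush, and the overall gain there is at most 4.1 points. The design assumption is about 14 points on the relative reading (25 on the absolute reading). At 10 to 14 points the strata are attenuated but positive.

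Nor can one infer that a spurious effect would probably be declared. In Model B the no-effect bias is under one standard error, and in both models it disappears if the route does not change blush. How the results would be reported is not something the protocol reveals.

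Finally, the models cover blush only. The IC bolus follows restoration of flow, so its influence on final TIMI flow could be smaller. The sizes above should not be carried over to subgroup 9.

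None of this rescues the structure. The bias arises exactly when the route affects flow or blush, which is what the trial sets out to show. It also cannot be put down to detail left for an analysis plan, because the protocol states the choice outright.

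**Conclusion.** The point holds as a structural fault in two of the ten planned subgroups. Items 9 and 10 are post-randomisation end points, so IC-versus-IV differences within them are not randomised comparisons. The analysis is literally circular where TIMI flow or blush is examined within its own strata. For blush, under the stated assumptions, expect attenuation in both strata if the overall gain is about 10 to 14 points. Expect a spurious difference of about -2 to -4 points (at most -8) if there is no effect on ST resolution, and no bias if the route leaves blush unchanged. The effect on subgroup 9 has the same form but unknown size. This should be fixed; it is not a threat to the main result.

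**What to change.** Remove items 9 and 10 from the list of subgroups for treatment effects. Alternatively, keep them under a separate label, either as non-randomised descriptive associations between flow or blush and ST resolution, or as a mediation or principal-stratum analysis with its assumptions written down.

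State that subgroup factors must be determined before the assigned treatment can affect them, with randomisation as the safe anchor. Item 7 needs a time point to qualify: the Coronary angiography section records thrombus among features taken at baseline, during and after the procedure, and the subgroup list does not say which reading applies. Specify the pre-procedural (baseline) angiogram.

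The cost is a few lines of text. No patients, data collection or sample size are affected, and no valid inference is lost.
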